**HISTORY OF PROTOCOL CHANGES**

Version 1.0, 15 Dec 2023

- None

## 1.0 ABSTRACT

Sub-Saharan Africa is home to the largest population of adolescents living with HIV (ALWH). Engaging ALWH in HIV care is challenging and reflected in lower rates of viral suppression and higher rates of loss to follow-up as compared to adults in the region. Depression has been identified as a significant barrier to initiating and remaining in HIV care. Indeed, this is the case for ALWH in Malawi where estimates of viral suppression range from 40%-78% and estimates of depression range from 18-26%. Resource-appropriate interventions that improve depression and address engagement in HIV care for ALWH are urgently needed.

The Friendship Bench (FB) is an evidence-based depression counseling intervention delivered by trained, supervised lay health workers. It is proven to reduce depression in the general adult population in low-resource settings but has not been adapted to be youth-friendly or enhanced with peer support to facilitate engagement in HIV care among ALWH. FB is based on problem-solving therapy, which offers an ideal framework for youth-friendly adaption and integration of retention peer support into a proven depression treatment model.

During the formative phase of this project, we conducted qualitative research to better understand how depression impacts HIV care engagement amongst ALWH. We used data gathered in the formative phase to adapt the existing, evidence-based FB protocol to meet the developmental needs of ALWH and to enhance the adapted protocol with peer support to facilitate HIV care engagement among ALWH.

In this second phase, we aim to conduct a 3-arm individual-level randomized pilot trial to determine the feasibility, fidelity, and acceptability of the Adapted and Enhanced FB protocols. The second phase is further working towards our long-term goal of adapting, testing, and scaling up resource-appropriate interventions to reduce depression and improve engagement in HIV care amongst ALWH.

## 2.0 BACKGROUND, PROBLEM STATEMENT, AND JUSTIFICATION

After conducting formative research on depression and HIV care engagement amongst ALWH, we generated evidence for the adaptation and enhancement of the existing, evidence-based FB protocols. This protocol aims to conduct a 3-arm clinic randomized pilot trial to compare the adapted FB and the enhanced FB to standard of care. This pilot trial is the next step towards reaching our long-term goal of adapting, testing, and scaling up resource-appropriate interventions to reduce depression and improve engagement in HIV care amongst ALWH.

### 2.1 Background and Literature Review

Sub-Saharan Africa (SSA) is home to the largest population of adolescents (10-19 years) living with HIV (ALWH). The 1.46 million ALWH in SSA account for 88% of all ALWH worldwide (1.65 million) and includes individuals who acquired HIV vertically (perinatally) and horizontally (behaviorally). This population is growing due to increasing survival of vertically infected children and increasing rates of horizontal infections among adolescents. In addition, adolescents are the only age group in which AIDS-related deaths are not decreasing in the region. This high burden of morbidity and mortality has led the Joint United Nations Program on HIV and AIDS, the World Health Organization, and NIMH to declare ALWH a priority population requiring immediate attention for research, programming, and policy.

Engaging ALWH in HIV care is critical for maximizing the impact of antiretroviral therapy (ART) on health outcomes, life expectancy, and secondary HIV transmission. The challenge of engaging and retaining ALWH in care is reflected in lower rates of viral suppression and higher rates of loss to follow-up for this group compared to adults and children in SSA. Indeed, such is the case in Malawi, where 3% of the adolescent population is living with HIV (75,000 of 2,257,834 individuals) and estimates of viral suppression among those on ART range from 40%-78%.

Poor engagement in care among ALWH has been attributed to the numerous psychosocial and structural challenges that arise from living with a stigmatized, chronic disease in a low-resource setting during a period of developmental transition - challenges that also increase the vulnerability of ALWH to mental health issues such as depression. Estimates of depression for ALWH in Malawi range from 18%-26%, and depression exacerbates poor engagement in care amongst ALWH. Consequently, addressing depression among ALWH may not only improve mental health but also ART adherence and viral suppression, affording improved individual health outcomes while also acting as secondary prevention among sexually active adolescents.

Growing literature, mostly involving adults, suggests that mental health interventions delivered by non-specialists in resource limited settings can improve depression outcomes. These task-shifting approaches are critical in countries like Malawi, which has few specialist options for the diagnosis and treatment of common mental disorders. Such task-shifting approaches often incorporate sociocultural frameworks and counseling therapy, moving beyond a purely biomedical approach to mental health. However, existing interventions incorporating these approaches have been largely developed for adult populations and there are few data demonstrating their effectiveness among adolescents, particularly ALWH, or if they impact ART adherence. Adolescence is a unique period of profound physical, cognitive, and social change where individuals begin to make health-related decisions independently but are still largely influenced by their family members, peers, and intimate partners. Navigating these developmental changes is further complicated for ALWH who face issues surrounding inconsistent support from their caregivers, negotiating safe sex, status disclosure to their social ties, stigma related to HIV, and barriers in accessing health services. In addition, the experience of ALWH differs based on how they acquired HIV: some adolescents have been managing a chronic disease since birth while others must learn to cope with a more recent infection. Considering these complex needs, there has been a global push for health interventions which are accessible, confidential, and developmentally appropriate, and which provide a safe space where adolescents can share sensitive concerns without judgement. Existing youth-friendly intervention models have largely focused on sexual and reproductive health rather than mental health. Taken together, improving depression outcomes and engagement in care among ALWH requires rigorously adapting and enhancing mental health interventions to address the adolescent population's unique needs--their mental health and HIV care engagement needs.

## 2.2 Problem Statement and Justification

The Friendship Bench, an evidence-based task-shifting counseling intervention that improves mental health outcomes in low-resource settings, is a superb candidate for such an adaptation. The Friendship Bench intervention was developed over 20 years of community research to provide lay health workers with the tools, training, and supervision to effectively address depression and other common mental health disorders in Zimbabwe. The Friendship Bench was originally intended for use in primary care clinics among the general adult population. Our team has led efforts to pilot test the expansion of the Friendship Bench for adults with HIV, patients with chronic disease, and perinatal women in Malawi and other researchers are currently adapting the Friendship Bench for HIV negative adolescents in Zimbabwe and Botswana. However, the intervention has not been adapted to address the specific needs of ALWH. Our team has also combined the Friendship Bench with ART adherence counseling based on cognitive behavioral therapy and motivational interviewing, using skilled counselors. In Malawi, skilled counselors are not widely available and are often middle aged. Thus, we propose to integrate HIV engagement support into the Friendship Bench intervention using simple, evidence-based peer-delivered strategies.

The Friendship Bench approach is based on problem-solving therapy principles. The Friendship Bench comprises 6 individual sessions delivered by trained, supervised lay counselors attached to a primary care clinic. The Friendship Bench uses problem-solving therapy to improve mental health outcomes by having counselors work with participants to identify a problem and possible solutions. The Friendship Bench was tested in a cluster-randomized controlled trial in 24 primary care clinics in Zimbabwe. At 6 months after intervention initiation, participants in clinics randomized to the Friendship Bench had fewer common mental disorders, depressive and anxiety symptoms, and disability severity, compared to those randomized to enhanced usual care.

Peer support is a proven approach for engaging adolescents and young adults in HIV prevention and treatment services. The positive impact of peer support on psychological wellbeing has been well documented among ALWH in SSA and has also been linked to better engagement in HIV care. Utilizing peer supporters is particularly salient for ALWH given the importance of peers for identity creation, acceptance, coping, and normative health behaviors during adolescence. In addition, previous interventions for ALWH have found that peer supporters are able to reach this population at their point of need in a confidential, safe manner and ensure that they are then linked to relevant services. Despite these benefits, few studies have mapped support networks of ALWH to understand gaps in sources and types of support, how support needs might vary between vertically and horizontally infected adolescents, what type of peer might be the best to provide support, and what type of training peers might need to meaningfully support emotional well-being, positive health behaviors, and increased HIV care engagement. In addition, there is little information on how peers can engage caregivers in their support activities given that caregiver support is also important for consistent engagement in HIV care for minors. Understanding these differences and needs is essential to developing and improving peer support strategies for engagement in care among ALWH.

The formative research generated critical evidence that has allowed us to adapt the FB protocol to meet the developmental and contextual needs of ALWH and enhance the adapted protocol with peer support to facilitate HIV care engagement. The Friendship Bench's problem-solving approach protocol makes it an ideal model to integrate retention in HIV care peer support. Our formative research identified the optimal peer support sessions to be in-person group format. By combining youth-friendly depression treatment with retention peer support, the eventual adapted and enhanced Friendship Bench protocols will address a range of challenges ALWH face during the transition to adulthood and lead to improved mental health and HIV care outcomes.

In this study, we will conduct a 3-arm clinic randomized pilot trial to compare the adapted and the enhanced FB protocols to standard of care. We will determine the feasibility, fidelity, and acceptability of the adapted and enhanced protocols. This pilot trial is the next step towards reaching our long-term goal of adapting, testing, and scaling up resource-appropriate interventions to reduce depression and improve engagement in HIV care amongst ALWH. Information gathered in this proposal will lead to an R01 application for a cluster randomized controlled trial of the adapted and enhanced Friendship Bench interventions to improve depression and engagement in HIV care among ALWH.

## 3.0 OBJECTIVES

### 3.1 Main Objective:

- To conduct a pilot trial comparing the Adapted and Enhanced FB protocols to standard of care in addressing depression and HIV care engagement amongst adolescents living with HIV (ALWH)

### 3.2 Specific Objectives:

- To determine feasibility, fidelity, and acceptability of the Adapted and Enhanced FB protocols
- To compare preliminary effectiveness of the Adapted and Enhanced FB protocols in reducing depression and improving engagement in HIV care

## 4.0 HYPOTHESES

There are no hypotheses given that the aim of the pilot trial is to assess feasibility, fidelity, acceptability, and preliminary effectiveness of the Adapted and Enhanced FB intervention.

## 5.0 LITERATURE REVIEW

See section 2.1.

## 6.0 METHODOLOGY

6.1 Design of Study: We will conduct a three-arm individual-level clinical pilot trial across four clinics. Clinics will be randomized either to adapted Friendship Bench (N = 35 ALWH), enhanced friendship bench (N = 35 ALWH), or standard of care (N = 35 ALWH). Participants will all be recruited and followed for 12 months.

The Adapted Friendship Bench (AFB) will be adapted from the existing Friendship Bench intervention protocol to be youth-friendly and address the unique needs of ALWH. Youth friendly adaptation will include selection of young counselors (mixed genders, aged 20-35) who are motivated to work with young people. Counselors will be trained to deliver non-judgmental counseling that respects the privacy and autonomy of ALWH and enables them to make free and informed choices that are relevant to their individual needs. Training will also include discussion of adolescent development and the unique experiences of ALWH related to stigma, disclosure, social relationship issues, and health care access. Counseling sessions will take place in a youth oriented but discrete location within the HIV clinic and be available on weekends to ensure accessibility. AFB will include 6 individual counseling sessions facilitated by counselors attached to one of the study HIV clinics. The first session includes three components called Opening the Mind, Uplifting, and Strengthening, with subsequent sessions building on the first. Opening the Mind refers to the therapeutic process by which, through asking questions, clients are encouraged to open their minds to identify their problems, choose one to work on, identify a feasible solution, and agree on an action plan through an iterative process guided by the counselor. Each structured session lasts 30-45 minutes and will be conducted in a private clinic room in the participant's local language (Chichewa). No specific retention support will be provided, but participants may identify barriers to engagement in HIV care to address during their counseling session. After 4 sessions of individual therapy, the counselor can refer participants not improving or with suicidal ideation to a supervisor trained in mental health to reassess and manage the case. Case management may include additional counseling or pharmacotherapy, at the discretion of the managing clinician.

The Enhanced Friendship Bench (EFB) will include all elements of AFB but will additionally integrate peer support via in person group meetings to facilitate engagement in care for ALWH and depression. Peer supporters will be mature young adults (aged 18-21) who have completed secondary school, are openly living with HIV, and motivated to work with adolescents. The counselors must be willing to maintain participant and colleague confidentiality and sign a confidentiality agreement. Peer Supporters will be trained to deliver youth-friendly group sessions related to HIV care. The content of the 6 peer support sessions includes: Mental Health and HIV, Status Communication, Adherence and Viral Load Testing, Secondary Prevention (Sex and Relationships), Stigma, and Planning for the Future. The 6 sessions will be delivered monthly over 6 months and last 90 minutes each. The group sessions will be in a private space in the clinic in the participant's local language (Chichewa).

Standard of Care (SOC) for mental health in public facilities in Malawi includes options for basic supportive counseling by the primary provider or nurse, medication management by the primary provider, referral to the clinic psychiatric nurse or mental health clinic (most clinics have either an assigned psychiatric nurse or a mental health clinic that visits on a rotating basis), or in more severe cases referral to the psychiatric units at tertiary care hospitals (in the Lilongwe region, this is Bwaila Hospital). For this study, standard care will be enhanced by a trained study nurse who will provide mental health evaluation; brief supportive counseling; information, education, and support on depression; and (if indicated) facilitation of referral to the clinic's psychiatric nurse or mental health clinic or to Bwaila Hospital. The study nurse will have up to 3 follow-up contacts with the participant to assess whether they have followed up on recommended referrals or treatment plans and to assess whether any further outreach is indicated.

**6.2 Place of Study:** The participating health centers will be the Area 18, Area 25, Kawale, and Lighthouse Health Centers. These sites are all government health facilities located in urban Lilongwe, Malawi with ART clinics on their grounds. We selected clinics well matched in terms of staffing levels, services offered, NGO/ancillary program involvement (e.g., all three sites receive training and supervision support from the Lighthouse Trust NGO in Lilongwe), patient volume, and patient population to minimize any important differences between the sites. UNC-Project Malawi will serve as the administrative home for the study and has longstanding relationships with all 4 proposed study sites. UNC Project-Malawi has previously successfully recruited and enrolled adolescents in several sexual and reproductive health studies as well as HIV-related clinical trials.

**6.3 Target Population: ALWH:** We will recruit 105 ALWH from 4 HIV clinics in Lilongwe, Malawi. We aim to recruit for diversity in age, gender identity, and HIV acquisition type. ALWH will be eligible for the study if they are: (1) age 13-19; (2) diagnosed with HIV; (3) scored  $\geq 13$  on the self-reported BDI-II; (4) willing to provide consent (age 18 or 16-17 years old and married (emancipated minors per Malawi law) or assent with parental consent (age 13-17). All HIV+ individuals will be eligible for recruitment including ART initiators, ART re-initiators and established patients. ALWH screening positive for depression who choose not to participate will be referred to a mental health provider.

Feasibility of ALWH Recruitment: The proposed study will be conducted at 4 comparable, public health centers in Lilongwe District, Malawi: Area 18, Area 25, Kawale, and Lighthouse. Each of the 4 health centers provides ART services, is located in the urban or peri-urban areas of Lilongwe on a main road, and has a monthly ART clinic volume > 115 individuals (age 10-19) who are either initiating care or established patients. We expect 90% will be between the ages of 13-19. Based on studies among ALWH in Malawi, we conservatively estimate 18% will have depression. Assuming an 80% participation rate, enrolling ~6 ALWH presenting with depression (age 13-19) per site per month (35 ALWH total per site) is feasible in 3 months for a total of 105 ALWH in the entire study. Though current government led data collection efforts for ART care in Malawi include adolescents aged 10-19 and our proposed study includes adolescents in a smaller age window (age 13-19), we believe that our conservative recruitment efforts account this mismatch.

Psychosocial Counselor Recruitment: We will recruit 3 young individuals to be psychosocial counselors at each clinic who will provide the 6 individual counseling sessions to participants (approximately 70 sessions per counselor over 4-6 months). Peer Supporter Recruitment: We will recruit 3 peer supporters for the Enhanced FB arm from the Community Advisory Board, Baylor Teen Club Graduates, and YFHS Clinic Experts. We will aim to select peer supporters who are varied in age, gender, and HIV acquisition status. Supervision for the peer supporters will be provided by the study coordinator.

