#### 6.4 Sampling Techniques and Tools

We will recruit ALWH from 4 HIV clinics in Lilongwe, Malawi and each clinic will be randomized to the adapted Friendship Bench, Enhanced Friendship Bench, or standard of care.

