To assess balance across all 3 study arms at enrollment, we will compare participant characteristics using t-tests for continuous variables and chi-square tests for categorical variables. Quantitative Data: Quantitative measures of feasibility, fidelity, acceptability, and preliminary effectiveness will be summarized using means and standard deviations or proportions and compared across arms using statistical models for continuous or binary outcomes, as appropriate. For feasibility, we will examine the mean number of ALWH enrolled and the proportion of ALWH retained in each of the three study arms (adapted, enhanced, and standard of care). For fidelity, we will examine and compare the proportion of counselors covering at least 80% of checklist items during random direct monitoring sessions across study arms. For acceptability, we will examine and compare the proportion of participants and study staff who found the intervention helpful and easy to deliver across study arms. Changes in depression and engagement in care will be assessed for the 6-month study visit and the 12-month study visit. Generalized estimating equations with an appropriate link for each outcome (i.e., identity link for continuous variables and log link for binary variables) and an exchangeable correlation matrix will be used to examine differences in BDI-II scores, engagement in care, and viral suppression and will account for baseline values of all outcomes and clinic differences. All statistical models will control for any unbalanced confounders. Every effort will be made to minimize missing data, including collecting detailed locator information for the participant as well as for up to two individuals who could help reach the participant should they drop out of contact. However, some missing data is likely to occur. We will examine the data for patterns of missingness and if identified, will conduct sensitivity analyses using inverse probability weights to correct for the bias introduced by the missing data. Qualitative data: Analysis of qualitative exit interview data will involve four steps: 1) reading for content; 2) deductive and inductive coding; 3) data display to identify emerging themes; and 4) interpretation. Codes will be refined during the analysis process and memos will be written for each identified theme.

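### The protocol names two units of randomisation, individual and clinic; if clinics are the unit, four clinics in three arms confound arm with clinic and the planned between-arm comparisons lose their basis

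*Protocol*

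**What the plan says.** On the unit of randomisation, the protocol gives two answers.

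- **Individual.** The abstract (1.0) describes a "3-arm individual-level randomized pilot trial". The first sentence of 6.1 also calls the trial individual-level, across four clinics.
- **Clinic.** The next sentence of 6.1 reads "Clinics will be randomized either to adapted Friendship Bench (N = 35 ALWH), enhanced friendship bench (N = 35 ALWH), or standard of care". Section 2.0 says "This protocol aims to conduct a 3-arm clinic randomized pilot trial to compare the adapted FB and the enhanced FB to standard of care", 2.2 says "we will conduct a 3-arm clinic randomized pilot trial", and 6.4 says "each clinic will be randomized to the adapted Friendship Bench, Enhanced Friendship Bench, or standard of care".

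On sites, 6.2 and 6.3 name four clinics and a total of 105. Section 6.2 also refers to three sites when describing NGO support. The recruitment paragraph of 6.3 gives 35 participants per site and still totals 105. It also plans three counselors at each clinic, with about 70 sessions per counselor.

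On analysis, 6.7 compares primary and secondary outcomes across the three arms. The effectiveness outcomes use generalized estimating equations (GEE) with an exchangeable correlation matrix, in models that "will account for baseline values of all outcomes and clinic differences".

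**The concern.** The unit of randomisation decides what the arm comparisons mean. Staff following the abstract and staff following 6.4 would run different trials.

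If clinics are allocated, a participant's arm is fixed by the clinic attended. Any difference between arms in retention, BDI-II or viral suppression is then also a difference between clinics. Adjusting for clinic, as 6.7 intends, would remove the very contrast that the comparison needs. No analysis can repair this once clinics have been allocated, so it has to be settled in the protocol.

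**Working it through.** **1. Which reading do the protocol's own figures fit?**

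- Per-site enrolment (6.3): 35 × 4 = 140, but 35 × 3 = 105. The stated total fits three sites, in line with the three-site remark in 6.2.
- Counselor workload (6.3): one clinic of 35 participants, 6 sessions each, 3 counselors gives 35 × 6 / 3 = 70, the stated figure. With individual randomisation over four clinics, 70 Friendship Bench participants and 3 × 4 = 12 counselors give 70 × 6 / 12 = 35.

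The workload therefore fits one whole clinic per Friendship Bench arm. The abstract, the opening of 6.1 and the four named clinics do not sit with that. The figures do not settle the question.

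**2. The stated precision (6.5).** The half-width is 1.96 × √(p(1−p)/n), with independent participants and no design effect.

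- n = 35: 16.6 points at p = 0.50 and 9.0 at p = 0.92. The stated 9–17 is reproduced for p of about 0.50 to 0.92.
- n = 105: 9.0 points at p of about 0.67 and 7.0 at p of about 0.84. The stated 7–9 is reproduced only in that range.

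The protocol gives no proportions, so this match is conditional. Both ranges are of the size expected without clustering.

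**3. Can arm contrasts be estimated?** Take an intercept, 2 arm terms and 3 clinic terms: 6 columns.

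- *Clinics randomised, arms of 2 + 1 + 1 clinics.* Let the two-clinic arm be the reference. Each of the other two arm indicators then equals the indicator of its only clinic. The rank is 4 of 6, and the clinic terms alone already have rank 4. None of the 3 arm contrasts is estimable.
- *Same allocation, clinic terms dropped.* All 3 contrasts can be computed. Between-clinic degrees of freedom are 4 − 3 = 1, so the two-sided 5% t critical value is 12.7 instead of 1.96.
- *Individuals randomised within four clinics.* The rank is 6 of 6, and all 3 contrasts are estimable with clinic in the model.

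**4. Size of the error if clinic is ignored.** Compare two arms, each one clinic of 35, with no true effect. With total variance 1, a clinic mean has variance ICC + (1−ICC)/35, while a test that ignores clinic uses (1−ICC)/35. The ratio is 1 + 35·ICC/(1−ICC), and the type I error is 2·[1 − Φ(1.96/√ratio)]. The protocol gives no ICC, so the values below are assumptions.

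| Assumed ICC | Variance ratio | Type I error at nominal 5% |
|---|---|---|
| 0.01 | 1.35 | 9.2% |
| 0.02 | 1.71 | 13.4% |
| 0.05 | 2.84 | 24.5% |

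**The case against.** The strongest defence is that this is a pilot. Section 4.0 states no hypotheses, 6.7 makes feasibility, fidelity and acceptability primary, and 6.5 sizes the study on precision rather than power. Those outcomes can be described arm by arm under either reading. That stands, and it limits the damage to comparisons. It does not remove the damage: 3.2 sets an objective of comparing preliminary effectiveness, and 6.7 specifies models for it.

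The clinics are described in 6.2 as well matched, and baseline values enter the models. Both may lower the relevant ICC and so the error rates above. Neither separates arm from clinic or adds degrees of freedom, and 6.7 itself expects clinic differences.

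Three stronger readings are tempting and are not supported:

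- *Arm and clinic are identical, so no arm effect can be estimated.* Clinic is nested in arm, and if all three arms are used one arm has two clinics. Unadjusted differences can be computed; what fails is attributing them to the arm.
- *The planned GEE cannot be fitted.* That assumes clinic fixed effects. Section 6.7 does not say how clinic differences enter, or whether the exchangeable correlation is within participant or within clinic. An analysis plan not shown may say. Clinic as the GEE cluster would leave only 4 clusters, too few for credible standard errors.
- *The numbers show that individual randomisation was meant.* The figures of 35 per site, three sites and 70 sessions point the other way, towards one clinic per arm.

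Clinic allocation is also a defensible thing to pilot, since 2.2 says that a cluster randomised trial is to follow.

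**Conclusion.** The contradiction is explicit in the current text and extends to the number of sites. Its consequence is conditional. If individuals are randomised within clinics, every arm contrast is estimable and only the text and staffing figures need correction. If clinics are randomised and every arm receives at least one, at least two arms rest on a single clinic and arm is confounded with clinic. The comparisons in 6.7 then cannot deliver what is planned: no contrast is estimable with clinic fixed effects, and 1 between-clinic degree of freedom remains without them.

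The aliasing result needs no ICC. The error rates of 9.2% to 24.5% rest on assumed ICCs of 0.01 to 0.05, apply to two single-clinic arms tested as though clinic did not matter, and concern inference beyond the particular clinics. Within-arm description is unaffected. This must be resolved, because it determines what the trial may conclude about differences between arms.

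**What to change.** State one unit of randomisation and one number of sites, and bring 1.0, 2.0, 2.2, 6.1, 6.2, 6.3, 6.4 and 6.7 into line. Either choice is workable.

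- **Individuals.** Randomise with concealment within each clinic and keep clinic as a stratum in the GEE. Replace the clinic-randomised wording in 2.0, 2.2, 6.1 and 6.4. Restate per-site enrolment, sessions per counselor (35 on the present staffing, by the arithmetic above) and the peer-group arrangements. The cost is a risk of contamination within clinics and small peer groups: 35 / 4 is about 9 Enhanced Friendship Bench participants per clinic, with three peer supporters planned for the arm.
- **Clinics.** Correct the individual-level wording in 1.0 and 6.1, and say which arm receives the second clinic and how many participants each clinic enrols. Remove the clinic adjustment and the between-arm tests from 6.7, report arms descriptively, and state that arm and clinic effects cannot be separated. The cost is weaker claims only.

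Both need a protocol amendment. The protocol does not give enrolment status; if clinics have already been allocated, only the second route remains.
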